### 4.3 Implications for Participants

Each participant will be required to contribute time to visit the allocated trial centre on eight occasions over a 65-week period.

- Screening consultation
- Baseline consultation
- 2-week telephone review of adverse events
- 4-week review
- 13-week review
- 26-week review
- 39-week review
- 52-week review
- 65-week review

The first occasion will involve a comprehensive consultation and health check-up with the principal investigator and a medical practitioner responsible for trial screening (including establishment of the diagnosis). Participants who do not fully meet the inclusion criteria will not be included in the study and will be notified of this outcome and any abnormal findings/test results from the screening. Their family doctors may also be contacted if the nature of these findings warrants this.

Subsequent visits for review and medication collection will be briefer. On five occasions (not at 0 and 65-week review), the participants will be required to have a blood sample taken, which may involve brief discomfort but poses no significant health risks. Participants will need to refrain from caffeine and smoking on the morning before blood testing and avoid alcohol and exercise for 24 hours prior to testing. Participants will be reimbursed up to \$30 for travel expenses and/or the time spent at each visit. In accordance with the above-mentioned ethical guidelines, a placebo will be utilised in this trial because there is no currently effective alternative medication for treatment of VaD. In addition, participants will continue to take their current prescribed medication.

A subset of 50 participants will undergo MRI scans. MRI scanning does not cause any pain, and the magnetic fields are not known to produce tissue damage of any kind. Some participants may experience discomfort when in an enclosed space or may find the noise of the scanner during

testing loud. Earplugs will be provided to prevent problems with noise and participants are able to communicate with the technician throughout the procedure. These participants will also be reimbursed for their travel expenses to the MRI centre.

Participants will be insured for their involvement in clinical research through Western Sydney University.

#### 4.4 Informed Consent

The protocol of informed consent will be conducted according to guidelines and appropriate national regulations outlined in Section 4.1. Although colleagues may introduce the project to potential participants, the principal investigators must provide written information and verbally discuss the trial with each person.

Informed consent will involve detailed provision at the appropriate level of comprehension for each person, about the purpose, methods, demands, risks, inconveniences, discomforts, benefits and possible outcomes of the research. Each person must exercise voluntary choice to participate, without coercion or inducement and recognise their choice will not impact on their relationships with the research team or their ongoing health management, and be informed that they are free to withdraw from the trial at any time.

The principal investigator will determine the participant's capacity to consent at the screening visit via a discussion of the trial process, and their understanding of it. Both written and verbal explanations of the trial process will be given. For individuals unable to provide personally signed and dated informed consent, guardians/carers of participants with cognitive impairment will be approached to provide consent on the participant's behalf. The person responsible for a participant must meet the legislation and guardianship regulation requirements applicable to the State or Territory in which the trial is being conducted. The person responsible will also be given written and verbal explanations of the trial process and asked to provide written informed consent.

During the screening visit, the investigator must advise the participant and their carer of the possibility that the participant's capacity to consent or participate in research may vary or be lost entirely. This matter will be discussed so the researchers can determine what course of action is to be taken at such times, and whether a person responsible is to be appointed to provide consent on the participant's behalf. It is important that the investigators agree to comply with the participant's wishes; unless these circumstances would prevent the investigator acting in the participant's best interest. The capacity to consent must also be considered at the end of the

study, where the participant is due to complete the full 65-week study and is seeking to continue with the post-trial intervention. The principal investigator will determine whether it is safe for the participant to be administered this medication, and whether they have the capacity to consent to the process. In cases where the participant cannot provide consent, the person responsible will be contacted to discuss the nature of this post-trial intervention and provided with the option to consent for this medication on the participant's behalf.

The participant (or person responsible where required), study partner/carer, and the principal investigator will sign two informed consent forms: one for the investigator and one for the participant to keep, in addition to their information sheet. The consent form will state the name and contact details for the principal investigator and study co-ordinators for each recruitment site, who are to be available 24 hours a day, if they have questions or concerns.

It is not envisaged that culturally sensitive issues other than those potentially encountered in the day-to-day running of a clinic would present. All personnel involved in the trial are experienced with conducting clinical practice and clinical research such that cultural needs and beliefs are recognised. If the consenting individual is unable to read the information provided, an impartial witness will be asked to observe the verbal discourse of the trial and witness the signing of the consent form.

#### **4.5 Anonymity/ confidentiality/ privacy**

In accordance with ethical guidelines, the anonymity, confidentiality and privacy of participants will be protected.

The electronic clinical trial management data system and all electronic data will be password protected. Hardcopy source data records will be kept in a locked cabinet in the office of the principal investigator at each recruitment site during data collection and at completion of the study. Western Sydney University will keep source or certified copies and electronic data for an indefinite period of time.

All publication material will refer to general trial results as aggregate data and no individual participant names or identifying information will be released.

Participants are welcome to view their personal data at any time during the trial.

## **5. ANALYSIS**

### **5.1 Outcome Measures**

The outcome measurements to be employed in this study are:

### Primary

- *Cognitive Test:* The Vascular Dementia Assessment Scale cognitive subscale (VaDAS-cog) will be used as the primary outcome measure of cognitive function in this trial. VaDAS-cog is modified version of the Alzheimer's Disease Assessment Scale cognitive subscale (ADAS-cog), which is a sensitive psychometric scale for assessing the severity of cognitive impairment over time in dementia participants and covers four core symptoms of dementia: memory, orientation, language, and praxis. VaDAS-cog comprises additional frontal lobe subtests covering attention, working memory, executive function and verbal fluency to reflect the unique pathological feature of VaD.
- *Functional Test:* Alzheimer's Disease Co-operative Study Activities of Daily Living Inventory (ADCS-ADL) is a validated instrument for assessing the level of functional disability in dementia patients and is gaining popularity in clinical trials for dementia. ADCS-ADL scale is largely comprised of basic activities (B-ADL) and instrumental activities (I-ADL). B-ADL are simple activities (eating, walking, toileting, bathing, etc), whereas I-ADL are more complex activities (using the telephone, preparing a beverage or meal, using household appliances etc).

### Secondary

- *Global Assessment of Change:* Clinician's Interview Based Impression of Change-plus (CIBIC-plus) is a reliable tool to rate participant's condition by a clinician experienced in the management of patients with dementia (global assessment). CIBIC-plus is a semi-structured interview and include four categories for evaluation – general, mental/cognitive state, behaviour and activities of daily living. It is estimated to take 30-45 min to complete.
- *Additional Executive Function Tests:* Small vessel disease that causes subcortical ischemic impairments, including lacunar infarcts and ischaemic white-matter lesions, is the most common type of vascular dementia in elderly people. Executive dysfunction, together with slowness of mental processing, early motor disturbances, and behavioural disorders are the main symptoms of vascular dementia. In this study, two additional instruments are employed for the further assessment of the executive function including CLOX and EXIT-25. Both instruments have been validated in various dementia cohorts including vascular dementia.

- CLOX: CLOX is a modified version of a clock drawing task and has been proven to be quick and sensitive tool for the assessment of executive function in elderly dementia patients. It has also been used a rapid method for dementia screening as it shows strong correlations with other traditional cognitive measures.
- EXIT-25: EXIT-25 was developed by the same group of researchers who developed CLOX with the aim to define the behavioural sequelae of executive cognitive dysfunction in dementia patients. It contains a 25-item interview scored from 0-50 and takes 15 minutes to complete. EXIT-25 correlates well with other executive control function tests such as Wisconsin Card Sorting Test.
- *Quality of Life Assessment:* DEMQOL is recognised as one of the best dementia-specific health-related quality of life (HRQOL) instruments for mild to moderate dementia (MMSE  $\geq 10$  is ideal for the target cohort in this study). DEMQOL has both self- (28-item DEMQOL) and proxy- rating (31-item DEMQOL-Proxy) components providing different but complementary perspectives on quality of life in dementia. DEMQOL also shows comparable psychometric properties to the best available dementia-specific measures.
- *Neuropsychiatric Inventory-Clinician rating scale (NPI-C)* is a revised version of the Neuropsychiatric Inventory (NPI). The latter is a popular assessment tool for neuropsychiatric symptoms based on a structured interview with a caregiver and comprises 10 neuropsychiatric domains including delusions, hallucinations, depression/dysphoria, anxiety, agitation/aggression, euphoria, dis-inhibition, irritability/lability, apathy, aberrant motor activity and night-time behaviour disturbances. The NPI-C includes additional items, and a clinician-rating methodology and has demonstrated inter-rater reliability and convergent validity in dementia participants.
- *MRI Neuroimaging Assessment:* Neuroimaging MRI has increasingly been used in the study of healthy and impaired human cognitive functions associated with neurodegenerative disorders. A significant correlation has been shown between MRI activity and ADAS-cog performance in patients with early Alzheimer's disease. Participants who agree to undergo MRI scanning will be asked to attend two MRI visits to investigate brain changes pre- and post-treatment/placebo (i.e. baseline and 12 months). Each test lasts approximately one hour. The following outcome measures will be assessed in the study:
  - A) volumetric changes of both treatment and placebo groups in 12 months by using 3D T1- and T2-weighted MRI scans (including pre- and post-Gd T1 scans). Both T1-

weighted and T2-weighted scans will be used as inputs for a multiple-channel segmentation algorithm for an increased accuracy of the computation. Post-Gd T1-weighted scans have better grey/white matter contrast and using both scans acquired in the same session will further improve the robustness and accuracy of volumetric estimation.

- B) Changes of white matter lesions by examining the volumetric changes of white matter hyperintensity (WMH) by using our own WMH pipeline.
- C) Cerebral microbleeds and progress using SWI.
- D) Detailed white matter mapping and change of network properties using DWI scans and diffusion tensor imaging (DTI) analysis using DWI scans will be conducted.
- E) Accurate cerebral blood flow (CBF) and volume (CBV) will be calculated using Gd perfusion scans and to investigate changes of CBF/CBV of treatment and placebo participants. CBF measures how quickly is blood flowing through tissue, in units of mL/100g/min and CBV is the concentration of blood in a tissue, classically measured in units of mL/100g. Perfusion weighted Imaging Tools will be performed to process Gd perfusion scans.

Analysis: Seven grey matter volumetrics will be taken into consideration in the 2 time-point data analyses, i.e. total brain grey matter volume, volumes of 4 cortical lobes, hippocampal volume and total subcortical volume. Three WMH measures will be included, i.e. total brain WMH, periventricular WMH and deep WMH volumes. One cerebral microbleeds measure, i.e. the count of microbleeds seen in the brain will be included. Further examination of 10 Gd perfusion variables, including 5 CBF (and CBV), i.e. CBF (and CBV) measures of 4 lobes and CBF (CBV) of hippocampus will be conducted.

### Safety Measures

- *Liver and renal function, and routine haematological and coagulation (PT, APPT and fibrinogen) tests* will be conducted at baseline, 4, 13, 26, 39 and 52 weeks after the commencement of the treatment.
- All adverse events will be recorded at each visit, including those suspected to be related to the treatment (such as headache, dizziness, vomiting, allergy, etc) and any worsening of symptoms will be closely monitored. An assessment of the relationship between the adverse events or abnormal test results and the treatment will be made by the chief investigators and

trial physicians. An adverse event will be followed up until it resolves or for up to a month after the study is concluded. Serious adverse events (SAEs) will be immediately reported to the Human Research Ethics Committee granting approval and Suspected Unexpected Serious Adverse Reactions (SUSARs) to the TGA, in accordance with their guidelines. The causality of SAEs will be thoroughly investigated.

| Week                                                     | -2 to 0          | 0                                | 2  | 4  | 13 | 26 | 39 | 52            | 65               |
|----------------------------------------------------------|------------------|----------------------------------|----|----|----|----|----|---------------|------------------|
|                                                          | Screening | Baseline                  |    |    |    |    |    | End Tx | Follow up |
| Window                                                   |                  | 0                                | ±3 | ±7 | ±7 | ±7 | ±7 | ±7            | ±7               |
| Initial neurological assessment                          | X                |                                  |    |    |    |    |    |               |                  |
| Medical History                                          | X                |                                  |    |    |    |    |    |               |                  |
| Vital signs (HR, BP, Ht, Wt)                             | X                |                                  |    | X  | X  | X  | X  | X             |                  |
| Physical Exam                                            | X                |                                  |    |    |    |    |    |               |                  |
| NINDS-AIREN diagnosis                                    | X                |                                  |    |    |    |    |    |               |                  |
| MMSE                                                     | X                |                                  |    |    |    |    |    |               |                  |
| GDS                                                      | X                |                                  |    |    |    |    |    |               |                  |
| Inclusion/Exclusion criteria                             | X                | X - checked before randomisation |    |    |    |    |    |               |                  |
| VaDAS-cog                                                |                  | X                                |    |    |    | X  |    | X             | X                |
| ADCS-ADL                                                 |                  | X                                |    |    |    | X  |    | X             | X                |
| CIBIC-plus                                               |                  | X                                |    |    |    | X  |    | X             | X                |
| NPI-C                                                    |                  |                                  |    |    |    | X  |    | X             |                  |
| CLOX                                                     |                  | X                                |    |    |    | X  |    | X             |                  |
| EXIT-25                                                  |                  | X                                |    |    |    | X  |    | X             |                  |
| DEMQOL                                                   |                  | X                                |    |    |    | X  |    | X             |                  |
| Haematology, coagulation, liver and renal function tests | X                |                                  |    | X  | X  | X  | X  | X             |                  |
| MRI scanning (if applicable)                             |                  | X                                |    |    |    |    |    | X             |                  |
| Adverse Events                                           |                  |                                  | X  | X  | X  | X  | X  | X             |                  |
| Con meds and procedures                                  | X                | X                                |    | X  | X  | X  | X  | X             |                  |

|                                 |  |  |  |  |   |   |   |   |  |
|---------------------------------|--|--|--|--|---|---|---|---|--|
| Compliance, success of blinding |  |  |  |  | X | X | X | X |  |
|---------------------------------|--|--|--|--|---|---|---|---|--|

Table 1. Data collection timeline

## 5.2 Statistical Analysis

### **Safety analyses**

There will be no interim analyses with the exception of monitoring safety variables. The frequency, type and probable association of adverse events will be tallied by de-identified treatment group every 3 months for review by the study team. If there is any significant safety issue identified an additional DMC meeting will be called.

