### 3. METHOD

#### 3.1 Study Design

This study will be conducted as a two-arm randomized, double-blind, placebo controlled clinical trial of 65 weeks, including a 52 week intervention and 13 week follow-up.

For a two-arm trial, participants will be randomized after informed consent is obtained, into two parallel treatment groups:

- a. Intervention group taking *SLT* (Active)
- b. Placebo control group (Placebo)

The trial will be double-blinded, such that the participants and investigators (including persons responsible for data collection, data management and data analysis) will not be aware of randomization assignments. No pilot study and no run-in period are required for this trial.

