### Randomisation and Allocation Concealment Protocol

Randomisation will be conducted external to the primary research team (investigators listed at the start of this document) by a research officer of the National Institute of Complementary Medicine (NICM). This person will be responsible for producing computer generated randomisation treatment sequences which randomly associate a randomisation number with either active or placebo treatment. NICM's Clinical Trials Manager and Strategic Operations Manager are responsible for securely storing the randomisation allocation in a restricted access electronic file.

Randomisation numbers will be allocated in permuted blocks of 6 randomisation numbers starting from 001 to 238 with each block containing 3 active and 3 placebo assigned randomisation numbers. Sites will allocate the randomisation numbers in order of number sequence starting with the lowest number in each block and using all numbers in a block of 6 before starting with the next block of numbers. As soon as the randomisation number is assigned, it will be recorded on the screening log, in the participant source data file and electronic Case

Report Form (eCRF). Details of any participants randomised out of sequence will be notified immediately to the Coordinating chief investigator.

Investigators and/or pharmacists may request to break the blind for a participant if there is a clinical need to know the treatment allocation for a subject e.g. to manage the treatment of a serious adverse event. The site's Principal Investigator needs to discuss the reasons for breaking the blind with the Coordinating Investigator (or if unavailable, the Trial Coordinator). If this request is approved, it will be forwarded to the NICM Clinical Trials Manager. The NICM Senior Manager and Clinical Trials Manager will liaise with the Chief Investigator to process the code break request. When a participant allocation blinding is revealed, the participant ID, date, reason for opening, name of person and signature of who broke the seal, should be provided in writing. The Principal Investigator, Chief Investigator and Statistician will be notified of this information. The participants, principal investigators, research team members, trial medical practitioners, data collection nurses and other staff of the trial centres will have no knowledge of the randomisation assignments until follow-up outcome measures and data analysis are complete.

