### 4.2 Safety and tolerability of interventions

Acute toxicity tests on *SLT* were undertaken in mice. The maximum tolerated dose (MTD) for the formula as whole, ginsenosides, flavone-glycosides and crocins was 1.7 g/kg, 4 g/kg, 1.3g/kg and 5.0 g/kg, respectively, all of which are significantly higher than the proposed clinical dose

(655x, 3422x, 1109x and 20486x respectively). A long term toxicity study was also conducted in dogs. The MTD of *SLT* is 200 mg/kg, which is 70 times higher than the clinical dose. In an *in vitro* study, the inhibitory capacity of *SLT* was evaluated on 5 cytochrome P450 isoenzymes recommended by the US FDA for drug interactions studies. The median inhibitory concentration (IC50) values for CYP1A2, CYP2B6, CYP2D6, CYP2E1 and CYP3A4 were 50-140-fold higher than those potentially achievable by the therapeutic doses. This indicates that *SLT* treatment is unlikely to cause significant herb-drug interactions.

Information about adverse events will be collected by means of a standard question at each visit: “Have you had any health problems since the previous visit?” and liver and renal function and routine haematological tests will be conducted at baseline, 4, 13, 26, 39 and 52 weeks after the commencement of the treatment. In addition, participants can contact the principal investigators in the event of concerning health problems. The investigators will contact the research physicians and/or other members of the research team, who will review the dosage and continuation status in the trial, provide medical advice and/or communication with their General Practitioner or other health professionals and co-ordinate emergency medical attention as is appropriate and required. Only in the event of discontinuation in the trial will the randomisation assignment for that participant be made known. If an adverse event is present when the clinical trial is terminated, its course will be followed until the event resolves or the investigator deems it to be unrelated to the trial and appropriate case management is organised.

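### Coded by-group adverse event tallies go to the study team every 3 months rather than only to the existing DMC, creating a risk of partial unblinding

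*Protocol*

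**What the plan says.** Section 5.2, Safety analyses, rules out interim looks except for safety: "There will be no interim analyses with the exception of monitoring safety variables". It then says that the number, kind and judged relatedness of adverse events "will be tallied by de-identified treatment group every 3 months for review by the study team". The DMC appears in the next sentence: "If there is any significant safety issue identified an additional DMC meeting will be called".

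The blinding commitments are broad. In section 3.1, "participants and investigators (including persons responsible for data collection, data management and data analysis) will not be aware of randomization assignments". In section 3.3, Randomisation and Allocation Concealment Protocol, the list of blinded people includes principal investigators and research team members, who "will have no knowledge of the randomisation assignments until follow-up outcome measures and data analysis are complete". The Treatment Protocol in section 3.3 repeats the commitment for investigating staff.

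Two passages describe how single assignments can become known during the trial. Section 3.3 allows an investigator or pharmacist to request a code break for clinical need. Details of any break go to the Principal Investigator, the Chief Investigator and the Statistician. Section 4.2 says: "Only in the event of discontinuation in the trial will the randomisation assignment for that participant be made known". It does not say to whom.

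**The concern.** A by-group safety table is comparative data, even under coded labels. Here it goes repeatedly to people whose judgements depend on the blind, while a body that could receive it instead already exists.

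Several judgements made during the trial are at stake. Section 5.1, Safety Measures, has the chief investigators and trial physicians judge causality. Those causality calls are then shown back by group, so an apparent pattern could shape later ones. Section 5.2, Missing data and protocol violations, has the study clinician determine, during the study, which deviations are serious enough to remove a participant from the per-protocol analysis. If outcome raters also belong to the study team, CIBIC-plus and NPI-C are exposed, since both rest on clinician judgement. Both are secondary outcomes.

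**Working it through.** The Protocol gives no figure for this point, so the check is mainly a comparison of passages. Two short calculations show the exposure.

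**1. Who sees what**
- Section 5.2, Safety analyses: the study team sees adverse events split by coded group.
- Section 3.1, and Randomisation and Treatment Protocol in section 3.3: investigators, data staff and research team members know no assignment until the end.
- Section 3.3, Randomisation: some assignments may be revealed by approved code breaks. The written details listed are the participant, date, reason and person, not the arm. But the requester has asked for the arm, and the Chief Investigator is involved in processing the request.
- Section 4.2: an assignment is made known on discontinuation.

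The first two are formally compatible, because a coded tally names no one's arm. Adding the last two shows how the protection could fail.

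**2. How a coded table could be decoded**
- There are two groups, hence two codes. Learning what one code means settles the other.
- The tally is by kind of event. Suppose a team member knows one participant's arm and that participant had an event appearing under only one code. That code is then identified.
- The match fails for common events that appear under both codes. It needs a distinctive event.
- If the same codes are used at the next review, that table is decoded too. The Protocol does not say whether the codes stay constant.

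**3. Number of reviews**
- One participant on treatment: 52 weeks / 13 weeks per review = 4.
- One participant to the end of follow-up: 65 / 13 = 5.
- Whole trial: 24 months of recruitment (section 3.3, Screening Appointment Protocol) plus 65 weeks, about 15 months, gives 39 months. 39 / 3 = 13. This assumes that recruitment keeps to plan and reviews run throughout.

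**4. Number of assignments that might become known**
- Section 3.2 plans for 30% non-compliance or withdrawal among 238 participants: 0.30 x 238 = 71.4, about 71.
- If section 4.2 were applied to all of them, about 71 assignments would become known. If to none, 0. The range is therefore 0 to about 71, and the upper end is an assumption. The 30% includes non-compliance, and section 4.2 may only limit when disclosure is allowed.
- The argument does not need the upper end. One suitable match is enough to decode a table.

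**The case against.** The strongest reply is that nothing is contradicted. The blinding passages promise no knowledge of assignments, and a coded tally reveals none. That is correct. A reader might infer that the plan openly unblinds the investigators, but the word de-identified in section 5.2 rules that out.

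A reader might also infer that an imbalance in expected events would identify the active group. The documents do not support that. In the multiple-dose Phase I study (section 2.3), adverse event proportions did not differ significantly from placebo, although only 24 volunteers took part. The events listed there and in section 4.2 are mostly non-specific. Both participants who withdrew from the pilot with insomnia or headache were on SLT, but two cases are no signature. An imbalance would support a guess, no more.

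Knowing which code is active still does not place a given participant in it. That needs a further link through the participant's own events.

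Nor is it shown that outcome raters see the tallies. The study team is undefined, and Appendix 4, item 5.1, lists raters separately from chief investigators, principal investigators and coordinators.

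The reference to an additional DMC meeting implies that others are scheduled, and the DMC's charter is not at hand. It cannot be said that the DMC lacks its own by-group review.

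Finally, the Protocol records the success of blinding at weeks 13, 26, 39 and 52. That could help detect a loss of blinding but would not prevent one.

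These points limit the concern to a risk. They do not explain why the study team needs the split tables.

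**Conclusion.** The point holds as a risk of partial unblinding. The Protocol chooses to send coded by-group safety data to the study team every 3 months, in a two-arm trial where single assignments can become known along the way.

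The size of any bias cannot be computed from the document. What can be stated is the exposure: about 4 reviews during one participant's treatment and about 13 over the trial as planned. Decoding a table through a known assignment requires three things: that assignment reaching a team member, a distinctive event, and a tally detailed enough to match it. Carry-over to later tables also requires unchanged codes. Any effect on CIBIC-plus and NPI-C requires raters to be among the recipients. No effect on either primary outcome is shown.

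**What to change.** - Send by-group tallies, coded or not, only to the DMC. Have them prepared by someone outside the blinded study team, for example the staff who already hold the allocation under the Randomisation section.
- Give the study team pooled tallies only. Let the DMC judge from the split data whether an additional meeting is needed.
- Reconcile the Randomisation section of 3.3, section 4.2 and Safety analyses in 5.2 on who may see individual assignments and group-split data. The sponsor and investigators must settle which disclosure rule on discontinuation is intended.

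The cost is mainly a change of recipient, since the DMC exists and non-team staff already hold the allocation. Data collection, sample size and significance level stay as they are. The study team loses its own between-group view of safety, but the DMC keeps it.
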